### Outcome measurements

2.8

#### CPR knowledge assessment

2.8.1

This section consists of nine multiple-choice questions covering fundamental CPR knowledge, airway opening and rescue breathing, and assessment of resuscitation effectiveness (10). Each correctly answered question is scored as 1 point, while unanswered or incorrect responses receive 0 points. The total score is the sum of all items, ranging from 0 to 9, with higher scores indicating better knowledge.

#### CPR skills assessment

2.8.2

CPR skills will be evaluated based on the assessment criteria developed by Zhao et al. (11). The evaluation includes eight components: environmental assessment, assessment of consciousness and activation of emergency medical services (EMS), recognition of cardiac arrest, patient positioning, chest compressions, airway clearance and opening, rescue ventilation, and the compression-to-ventilation ratio.

#### Self-efficacy (recognition and evaluation)

2.8.3

The Basic Life Support Self-Efficacy Scale, originally developed by ESC 365 (12) and culturally adapted into Chinese by Zhang et al. (13), will be used. The scale comprises three dimensions [recognition and evaluation, CPR performance, and safe use of an automated external defibrillator (AED)] with a total of 18 items. In this study, only the “recognition and evaluation” dimension will be used. Each item is rated on a 4-point Likert scale ranging from “strongly disagree” (1 point) to “strongly agree” (4 points). The Cronbach’s *α* coefficient for each dimension of the scale exceeds 0.80, indicating good internal consistency.

#### Behavioral intention

2.8.4

Behavioral intention to perform bystander CPR will be assessed using a scale developed by Zheng et al. (14). The scale includes four dimensions, of which only the behavioral intention dimension will be used in this study.

Items are rated on a 5-point Likert scale: “strongly disagree” (1 point), “disagree” (2 points), “uncertain” (3 points), “agree” (4 points), and “strongly agree” (5 points). The scale demonstrates excellent reliability, with Cronbach’s *α* coefficients exceeding 0.90 and split-half reliability greater than 0.80 across dimensions, indicating high internal consistency.

#### Course satisfaction (CSQ-3)

2.8.5

Participant satisfaction with the intervention will be assessed using the Client Satisfaction Questionnaire-3 (CSQ-3) (15, 16). This scale consists of three items designed to evaluate satisfaction with the received services, focusing on perceived quality, usefulness, and willingness to recommend the program to others.

The CSQ-3 has demonstrated good reliability and validity across different populations, with reported Cronbach’s *α* values typically exceeding 0.85. Each item is rated on a 4-point Likert scale, where 1 = strongly disagree and 4 = strongly agree. Higher scores indicate greater satisfaction with the program.

#### Skill retention rate

2.8.6

CPR skill retention will be assessed at 3 months post-training. The retention rate will be calculated as: retention rate (%) = (follow-up score/immediate post-training score) × 100%. This measure will be used to evaluate the long-term retention of CPR skills among middle school students.

### Blinding and assessment quality control

2.9

#### Blinding of participants and intervention providers

2.9.1

This study employed a cluster randomized controlled design. Participants were not informed of the specific differences between the study groups, such as whether they received simulation-based training or scenario-based role-playing training. However, intervention providers were aware of the intervention content and therefore could not be blinded. This limitation is inherent to the study design.

#### Blinding of outcome assessors

2.9.2

All outcome assessments were independently conducted by two emergency medicine instructors who had received standardized training. These assessors were not involved in group allocation, intervention implementation, or data management. In addition, they had no access to participants’ group assignments or previous assessment results during the evaluation process. Practical skills were evaluated using standardized scoring criteria, while questionnaire data were collected anonymously. Data entry, management, and statistical analyses were performed by designated research personnel who remained blinded to group allocation throughout the study.

#### Assurance of inter-rater reliability

2.9.3

Before the formal assessment, the two assessors underwent standardized training to ensure consistency in scoring. Ten CPR performance videos from individuals outside the study sample were used for pilot assessment. The intraclass correlation coefficient was calculated to evaluate inter-rater agreement, and an intraclass correlation coefficient of at least 0.85 was required before formal assessment. During the formal assessment, 5 % of the operation videos were randomly selected for repeat evaluation to monitor inter-rater reliability. If the intraclass correlation coefficient fell below 0.80, additional training and recalibration of the scoring criteria were conducted.

### Sample size calculation

2.10

This study is a two-factor factorial cluster randomized controlled trial, with “CPR knowledge and skills scores” as the primary outcome. Based on the literature, a significance level of 5% (*α* = 0.05) and a statistical power of 80% (*β* = 0.20) were adopted. Sample size estimation was informed by data from previous studies. It was assumed that the mean total CPR score (combined knowledge and skills score rate) would be 80% in the intervention group and 65% in the control group, with a standard deviation of 15% in both groups, corresponding to an effect size of *d* = 1.0. Assuming a 15% difference in the primary outcome (main effect), G*Power 3.1 was used for sample size calculation, indicating that a total of 128 participants would be sufficient for multivariate regression analysis (effect size = 0.25, power = 0.80, critical *F* = 3.921). Considering a potential attrition rate of 20%, the final minimum sample size was set at 160 participants. This study also takes into account the design effect resulting from the correlation among subjects within clusters. The design effect is calculated using the formula DE = 1 + (m − 1)*ρ*, where m represents the average number of subjects per cluster, and ρ represents the intracluster correlation coefficient (ICC) (17). In cluster randomized trials, the design effect is commonly used to adjust the sample size required for an individual randomized trial to the sample size required for a cluster-randomized design. The final minimum sample size for this study was set at 160 participants, which represents a 25% overall inflation factor added to the 128 participants required at the individual level. This inflation factor accounts for both the cluster-randomized design effect and the potential impact of dropouts or invalid data. Based on the average cluster size in this study and the ICC estimated from previous similar studies, the design effect did not exceed 1.25 (18). Therefore, after adjusting for the design effect, a sample size of 160 participants (selecting 4 classes, with 40 participants per class) would still provide no fewer than 128 valid cases, thereby meeting the requirements for testing the primary effect.

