Continuous outcomes will be analyzed using linear mixed-effects models. Binary outcomes will be analyzed using generalized linear mixed-effects models, and ordinal outcomes will be analyzed using ordinal logistic mixed-effects models. The models will include both fixed and random effects. Fixed effects will include the two intervention factors, time, the interaction between the two intervention factors, the interactions between each intervention factor and time, and the three-way interaction among the two intervention factors and time. When necessary, baseline outcome values and other prespecified covariates will also be included. Random effects will include a class-level random intercept to account for the correlation among students within the same class, as well as an individual-level random intercept to account for the correlation among repeated measurements from the same participant over time.

For repeated-measures data, within-participant correlation will be addressed through the inclusion of an individual-level random intercept. If the number of measurement time points and sample size allow, an unstructured covariance structure will be prioritized. If the model fails to converge or parameter estimates are unstable, compound symmetry or first-order autoregressive covariance structures will be considered as alternatives. The final model will be selected based on model fit indices and study design considerations. Model selection will consider the Akaike information criterion, Bayesian information criterion, model convergence, and the interpretability of parameter estimates.

Factorial effects will be analyzed according to the principle of interaction-first interpretation. For the primary outcome, the interaction between the two intervention factors and the three-way interaction among the two intervention factors and time within the repeated-measures framework will first be tested. If the interaction is statistically significant or shows a practically meaningful trend, simple-effects analyses will be conducted to estimate the effects of different intervention combinations at each time point. If no clear interaction is observed, the main effects of the two intervention factors will be interpreted. For intervention effects that vary over time, the interaction terms between intervention factors and time will be treated as key parameters for evaluating changes in intervention effects.

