Adjusted effect estimates and their 95% confidence intervals will be reported. For continuous outcomes, between-group mean differences or standardized effect sizes will be reported. For binary outcomes, odds ratios or relative risks with 95% confidence intervals will be reported. For ordinal outcomes, corresponding ordinal odds ratios will be reported. The intraclass correlation coefficient and design effect will be calculated to quantify clustering effects. The robustness of the results will be examined through per-protocol analysis and multiple imputation.

For missing data, the number, proportion, and reasons for missingness will first be reported by study group. If outcome data are missing, multiple imputation will be performed under the missing-at-random assumption. Each imputed dataset will be analyzed separately, and the estimates will then be pooled. To assess the potential impact of post-randomization differential attrition on the study conclusions, sensitivity analyses will be conducted. If there are apparent differences across study groups in intervention-period withdrawal rates, absence rates, intervention non-completion rates, or loss-to-follow-up rates, their potential contribution to selection bias and their possible influence on estimates of intervention effects will be discussed in the interpretation of the results.

Given that this is a pilot study, the sample size was primarily determined based on implementation feasibility. A lack of statistical significance in interaction tests will not necessarily rule out the presence of practically meaningful interaction effects. Therefore, the findings will be interpreted comprehensively by considering effect sizes, confidence intervals, intervention adherence, and implementation feasibility. All statistical tests will be two-sided, and a *p* value of < 0.05 will be considered statistically significant. Statistical analyses will be conducted using SPSS 27.0 and R 4.5.2 (packages lme4, emmeans, and mice).

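### The 80% power in 2.10 belongs to a 0.5 SD main effect with independent students; it matches neither the d = 1.0 stated beside it nor the interaction tests that come first, and 2.13 gives a different basis for N

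*Protocol article*

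**What the plan says.** Section 2.10 (Sample size calculation) assumes mean score rates of 80% and 65% with SD 15%, calls this d = 1.0, and labels the 15-point difference a main effect. It then gives the G*Power result: "indicating that a total of 128 participants would be sufficient for multivariate regression analysis (effect size = 0.25, power = 0.80, critical"; the value printed for the critical F is 3.921. It raises 128 to 160 for 20% attrition, says the same 25% inflation also covers a design effect of at most 1.25, and concludes that 160 students "would still provide no fewer than 128 valid cases, thereby meeting the requirements for testing the primary effect".

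Section 2.13 (Data analysis plan) sets the order of inference on the primary outcome and names what is to be tested at the start: "the interaction between the two intervention factors and the three-way interaction among the two intervention factors and time within the repeated-measures framework will first be" (the sentence is cut before its last word). A significant interaction, or a trend judged meaningful in practice, leads to simple effects at each time point. Main effects are interpreted only when no clear interaction is seen.

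The same section later states: "Given that this is a pilot study, the sample size was primarily determined based on implementation feasibility". It adds that a non-significant interaction does not necessarily exclude one that matters in practice.

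**The concern.** The printed power, the assumed effect and the order of testing do not fit together. The 80% goes with an effect half as large as the one described two sentences earlier. It also goes with the contrast that 2.13 reaches last. No power is given for an interaction or a simple effect, although the Abstract, 2.1 and the Discussion all present the interaction as a main purpose of the factorial design.

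The two accounts of N add to this. Section 2.10 presents a powered trial; 2.13 presents a pilot sized mainly by feasibility. The Abstract, Study aims, Study design and the limitations do not call the study a pilot. If both accounts stand, a positive result can be reported as coming from a powered trial and a negative one excused as coming from a pilot.

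**Working it through.** **Inputs.** From 2.10: alpha 0.05, power 0.80, f = 0.25, difference 15 points, SD 15, N = 128, attrition 20%, design effect at most 1.25. From 2.13: "All statistical tests will be two-sided". From the Abstract: four groups, 1:1:1:1, so 128 students are 32 per cell.

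**Step 1: reproduce 128.** Noncentral F with 1 numerator df, N − 4 error df and noncentrality N·f². At N = 128 this is 128 × 0.0625 = 8.0, the critical F(1,124) is 3.918 and power is 0.801. No smaller N reaches 0.80. The printed 3.921 matches 118 to 119 error df, so the numerator df is 1; N stays at 128 for models with 2 to 10 parameters. A 3-df test at the same f would need 179. The plan's figure is reproduced.

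**Step 2: put f in score units.** For a two-level main effect d = 2f = 0.5, and 0.5 × 15 = 7.5 points. The stated assumption is 15/15 = 1.0. At d = 1.0 a main effect needs only about 32 students in total (normal approximation), so d = 1.0 is not what produced 128.

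**Step 3: standard errors of the three contrasts,** in SD units, with independent students and one time point:

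- main effect (64 v 64): 2/√N = 2/√128 = 0.177
- simple effect (32 v 32): √(8/N) = √(8/128) = 0.250
- interaction (difference of differences): 4/√N = 4/√128 = 0.354

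The ratios are 1 : 1.41 : 2. An effect of 0.5 SD is therefore 2.83, 2.00 and 1.41 standard errors.

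**Step 4: allow for clustering as well as attrition.** 160 × 0.8 = 128 uses the whole inflation for attrition. If the design-effect ceiling also applies, the effective N is 128/1.25 = 102.4. Keeping an effective 128 would need 128 × 1.25/0.8 = 200.

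**Step 5: power** (noncentral t, N − 4 df, two-sided 0.05):

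| Effective N | Effect | Main | Simple | Interaction |
|---|---|---|---|---|
| 128 | 0.5 SD | 80.1% | 51.0% | 28.9% |
| 128 | 1.0 SD | >99.9% | 97.8% | 80.1% |
| 160 (no attrition) | 0.5 SD | 88.2% | 60.3% | 34.9% |
| 102.4 | 0.5 SD | 70.7% | 42.5% | 24.0% |

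Each row uses the same difference in score units for all three contrasts. An interaction entered as f = 0.25 has 80% power by construction, but it is a difference of differences of 1.0 SD, or 15 points. For 0.5 SD, 80% power needs about 256 students for a simple effect and about 508 for the interaction.

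Power for the three-way interaction with time cannot be computed, because the article gives no within-student correlation.

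**Step 6: the two rationales.** Section 2.10 derives 160 from 128 at 80% power and asserts adequacy for the primary effect. Section 2.13 says that feasibility was the primary determinant. One passage must yield to the other.

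**The case against.** The strongest reply is that 29% and 51% depend on choosing the 0.5 SD reading. The 7.5-point effect is printed nowhere; it is inferred from f = 0.25. At the 15 points that 2.10 does state, 128 independent students give 80% even for the interaction. This stands, so the power figures must be given for both effect sizes. It also means that the two sizes have to be reconciled before any power statement can be read.

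Second, sizing a 2 × 2 factorial on main effects is usual, and 2.10 labels its target a main effect. A reader might infer that the protocol claims 80% power for the interaction; it does not. What remains is that the adequacy statement sits beside an analysis that begins with a different test.

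Third, a reader might infer that the plan would take a non-significant interaction as proof of none. Section 2.13 says otherwise, and it asks for effect sizes and confidence intervals to be weighed. That caution is already there, but it gives no power and leaves the statement in 2.10 untouched.

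Fourth, the figures are for one time point and independent students, and should not be read as an upper bound. Baseline adjustment could raise them: with an assumed baseline correlation of 0.5, the 0.5 SD figures at N = 128 become about 90%, 63% and 37%. In the other direction, with one class per arm, class is confounded with cell, so the design does not secure independence.

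Finally, a reader might argue that the score ceiling makes synergy undetectable, by taking 65% as Group D and 80% as each component alone. Section 2.10 does not say which groups these means describe, and the argument would limit positive interactions only. It is not relied on here.

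**Conclusion.** The point holds in conditional form. The arithmetic behind 128 is right for a 1-df test at f = 0.25. As a main effect, this means 0.5 SD in independent students. The text around it is wrong as written in three respects: d = 1.0 and f = 0.25 are inconsistent as descriptions of the same main effect; the 80% does not describe the interaction tests that 2.13 puts first, or the simple effects that may follow; and 2.10 and 2.13 give conflicting grounds for N.

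Interaction power at N = 128 is 29% or 80% according to which of the plan's two effect sizes is meant. At 0.5 SD it is about 24% if attrition and the design-effect ceiling both apply. A flat statement that the trial has 29% power for its primary analysis would go further than the documents allow. All figures assume a single time point; those for N = 128 also assume independent students.

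**What to change.** In 2.10:

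- Reconcile d = 1.0 with f = 0.25 and state which difference the trial is meant to detect.
- Say that 80% applies only to a 0.5 SD main effect of one factor under individual-level independence.
- Give simple-effect and interaction power, conditional on the effect size and on independence: 51% and 29% at 0.5 SD, 98% and 80% at 1.0 SD.
- Remove the statement that the sample meets the requirements for the primary effect.

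Use one rationale for N in 2.10 and 2.13. The simplest is to keep the pilot and feasibility statement and present the G*Power result as an individual-level reference. In the Abstract and Discussion, describe conclusions about interaction or synergy as preliminary. The caution in 2.13 about a non-significant interaction can stay as it is.

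The cost is wording only, with no extra students, data or procedures. The stated power becomes less favourable.

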**Methods:**

A single-blind cluster randomized controlled trial with a 2 × 2 factorial design will be conducted in a middle school in Hohhot, Inner Mongolia Autonomous Region. A total of 160 eligible middle school students will be recruited and randomly assigned in a 1:1:1:1 ratio to four groups: conventional CPR training group, manikin-based training group, scenario-based drama review group, and combined manikin-based training plus scenario-based drama review group. Each training session will last 90 min. The primary outcomes are CPR-related knowledge score and skill performance score. Secondary outcomes include self-efficacy (behavioral performance and evaluation), behavioral intention, course satisfaction, and skill retention rate. Data will be collected at Baseline assessment (T0), immediate post-first training assessment (T1), 3-month post-first training assessment (T2), immediate post-second training assessment (T3), 3-month post-second training follow-up (T4).

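### The stated target in section 2.10 (15 points, SD 15, d = 1.0) is not the effect that yields 128 (f = 0.25, d = 0.5), and the score it uses is not a declared primary outcome

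*Protocol article*

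**What the plan says.** Section 2.10 (Sample size calculation) of the protocol article makes this assumption: "the mean total CPR score (combined knowledge and skills score rate) would be 80% in the intervention group and 65% in the control group". Each group is given an SD of 15%. The section states the standardised effect as d = 1.0 and labels the 15% difference the main effect. The next step is the G*Power result: "a total of 128 participants would be sufficient for multivariate regression analysis (effect size = 0.25, power = 0.80", with a printed critical F of 3.921. Nothing in the section connects d = 1.0 to 0.25. The 128 is then raised to 160.

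On the outcome, section 2.10 speaks of a primary outcome in the singular and sizes the trial on the combined score rate. The Abstract (Methods) says: "The primary outcomes are CPR-related knowledge score and skill performance score". Section 2.8.1 defines the knowledge score as a stand-alone total from 0 to 9, and section 2.8.2 describes the skills assessment separately. No part of section 2.8 defines a combined score, and section 2.10 gives no mean or SD for either score alone.

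On testing, section 2.13 (Data analysis plan) states: "All statistical tests will be two-sided", at the 0.05 level.

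**The concern.** A sample size justification should name one difference on one outcome and show that the number follows from it. Here the stated difference and the effect size entered differ by a factor of two, and the totals they imply differ nearly fourfold. A reader who takes the text at its word believes that the trial is sized for 15 points. A reader who works back from 128 concludes 7.5. Section 2.10 ends by assuring the reader that the requirement for testing the primary effect is met, and that cannot be judged until the target is settled.

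The choice of score adds to this. The assumed means and SD belong to a quantity that is not listed among the outcomes, so the quoted 80% power is not tied explicitly to either declared primary score.

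**Working it through.** **Inputs**
- Alpha 0.05 (section 2.10), two-sided (section 2.13), used here as an F test with 1 numerator degree of freedom.
- Power 0.80 (section 2.10).
- Means 80% and 65%, SD 15% (section 2.10).
- Four groups, 1:1:1:1 (Abstract, Methods), so each main effect compares two equal halves.
- Effect size 0.25 and N = 128 (section 2.10).

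**Formulas**
- d = difference / SD.
- f = d / 2 for two equal halves.
- Noncentrality λ = f² × N.
- Power = probability that a noncentral F with 1 and N − 4 degrees of freedom and noncentrality λ exceeds the 5% critical value.

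**Step 1. Reproduce the plan's figure.** With f = 0.25 and N = 128:
- λ = 0.0625 × 128 = 8.0
- critical F(1, 124) = 3.9175
- power = 0.8014

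128 is the smallest total that reaches 80%, so the figure is reproduced exactly.

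**Step 2. Convert back to points.** f = 0.25 is d = 2 × 0.25 = 0.5, and 0.5 × 15 = 7.5 points. As a cross-check, the normal approximation for 7.5 points at SD 15 gives 126 in total.

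**Step 3. Use the stated target.** d = (80 − 65) / 15 = 1.0, so f = 0.5. The smallest total is N = 34:
- λ = 0.25 × 34 = 8.5
- critical F(1, 30) = 4.1709
- power = 0.8054

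The normal approximation gives 32. With 128 participants, λ = 0.25 × 128 = 32 and power is 0.9999. All of these are individual-level figures, before clustering and attrition.

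**Step 4. Try other readings of 0.25.**

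| Reading | Total N for 80% power |
|---|---|
| Cohen's f = 0.25, 1 numerator df | 128 |
| Cohen's f = 0.25, 3 numerator df | 179 |
| Regression f² = 0.25, 1 tested term (matches d = 1.0) | 34 |
| Regression f² = 0.25, 2 tested terms | 42 |
| Regression f² = 0.25, 3 tested terms | 48 |

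Reading 0.25 as f² does recover d = 1.0, because 0.5² = 0.25, but it then gives 34 and not 128. None of these readings joins d = 1.0 to N = 128.

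**Step 5. Check the critical F.** F(1, 119) = 3.9208, which rounds to the printed 3.921. With four groups and five covariates, 128 − 4 − 5 = 119. Under that setting N = 128 has power 0.8011 and N = 127 has 0.7980, so 128 is still the smallest sufficient total. The number of covariates is an assumption; the article does not state it.

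**The case against.** The best defence is that 80% versus 65% was meant as the combined-training group against the control group. If the two components contribute equally and additively, each main effect is 7.5 points, f is 0.25 and 128 follows. The same holds if only the combined group reaches 80%: (80 + 65)/2 − 65 = 7.5. The first aim in section 1.2, which sets the combined model against conventional training, makes this a plausible intention. It does not rescue the text, because section 2.10 attaches the words main effect to the 15% difference. If this is what was meant, that label is the error and still has to be changed.

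It can also be said that a standardised calculation carries over to either primary score if the same standardised effect is assumed for it. That stands. It would be too strong to say that the 80% power applies to no planned test; the plan simply does not state the assumption.

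Four stronger readings are tempting, and the documents do not support them.
- **That the mismatch leaves the trial short of power.** It runs the other way: 128 exceeds what the stated target needs at the individual level.
- **That the printed critical F is wrong.** It fits an analysis with about five covariates. Section 2.10 describes a regression analysis and section 2.13 plans covariate adjustment.
- **That a 15-point target would leave ample room in 160 for clustering.** With one class per arm, a design-effect calculation says little about what the trial can support under either target.
- **That overall type I error is shown to be uncontrolled.** How two primary scores and two factors share alpha is a separate question. A protocol commonly leaves it to an analysis plan, which is not shown here, and any familywise figure would depend on how correlated the scores are.

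**Conclusion.** Section 2.10 is wrong as written. The stated main effect (15 points, d = 1.0, f = 0.5) needs 34 participants in total, whereas the reported 128 corresponds to half that effect (7.5 points, d = 0.5, f = 0.25). The ratio is 128/34, or about 3.8. This is an error of justification: it obscures which difference the trial is sized to detect and does not by itself reduce power. Separately, the calculation uses a combined score rate that section 2.8 does not define and that differs from the two primary outcomes in the Abstract.

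The conclusion assumes equal halves for each factor, a common SD of 15, a two-sided 0.05 test with one numerator degree of freedom, and independent observations. It takes no position on whether 160 is adequate once clustering is allowed for; that is a different point.

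**What to change.** Restate section 2.10 with one target that leads to the reported number. If 128 is kept, the target is a main effect of 7.5 points at SD 15 (d = 0.5, f = 0.25), before clustering and attrition. If 80% versus 65% was meant as the combined group against control, say so, remove the main-effect label from the 15 points, and state what each main effect is assumed to be. If 15 points really is the main effect, report the total that follows from f = 0.5 and explain why more participants are enrolled.

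Then reconcile the score with the Abstract. Either define the combined score in section 2.8 and declare it as the primary outcome, or base the calculation on the declared primary score or scores, with a mean difference and SD for each. Quote power for the test or tests that will actually be run. It would also help to state the number of covariates behind the critical F, although that figure need not change.

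The cost is a revision of wording and one re-run of the calculation. No change to the conduct of the trial follows from this point alone.

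### Section 2.10 spends the same 25% inflation (128 to 160) twice, on 20% attrition and on a design effect of up to 1.25; together they need 200, and 160 gives about 102 effective cases

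*Protocol article*

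**What the plan says.** Section 2.10 (Sample size calculation) takes 128 from G*Power with these settings: "effect size = 0.25, power = 0.80, critical *F* = 3.921". It then reaches its total by attrition alone: "Considering a potential attrition rate of 20%, the final minimum sample size was set at 160 participants".

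Further on, the section introduces the design effect, DE = 1 + (m − 1)ρ, and describes the step from 128 to 160 as a 25% inflation. Of that inflation it says: "This inflation factor accounts for both the cluster-randomized design effect and the potential impact of dropouts or invalid data". It puts the design effect at no more than 1.25, citing earlier studies for the ICC, but prints no ICC value. It concludes that, after adjustment for the design effect, four classes of 40 "would still provide no fewer than 128 valid cases, thereby meeting the requirements for testing the primary effect".

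The same section assumes score rates of 80% and 65% with an SD of 15%, which it labels d = 1.0.

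Section 2.13 (Data analysis plan) gives a different basis. It calls the trial a pilot and says that "the sample size was primarily determined based on implementation feasibility".

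**The concern.** An allowance for dropout and an allowance for clustering multiply. Dropout reduces how many students are measured; clustering reduces how much information each measured student carries. Section 2.10 has one increase of 25%, which dropout already accounts for exactly, and it assigns clustering to that increase as well. The closing claim of at least 128 cases after the design effect therefore appears to be a count of students rather than an effective sample size.

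At stake is the claim that the trial is adequately sized for its primary outcome. If it stands, a null main effect could be read as coming from a trial with 80% power, although the section's own inputs do not give that at the effect size it used. The feasibility statement in section 2.13 leaves the reader unsure which basis governs.

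**Working it through.** **Inputs, all from section 2.10 unless noted:** f = 0.25, power 0.80, N = 128; attrition 20%; total 160; DE = 1 + (m − 1)ρ; DE at most 1.25; four classes, m = 40; d = 1.0. Two-sided 5% tests come from section 2.13.

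**1. Reproducing 128.** Noncentral F test, numerator df 1, four groups, noncentrality λ = N·f². The smallest N with power of at least 0.80 at f = 0.25 is 128 (power 0.801). The critical F is 3.918 against the stated 3.921, a difference that does not matter here.

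**2. Reproducing 160.** 128/(1 − 0.20) = 160 exactly, and 160 × 0.80 = 128.

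**3. What is left for clustering.** With 20% attrition, the design effect that 160 can absorb is 160 × 0.80/128 = 1.00. With a design effect of 1.25, the attrition that 160 can absorb is 1 − (128 × 1.25)/160 = 0%.

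**4. Both in sequence.** 128 × 1.25/0.80 = 200, against the stated 160.

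**5. What 160 gives at the stated limits.** Effective sample = 160 × 0.80/1.25 = 102.4. At f = 0.25, λ = 0.0625 × 102.4 = 6.4, and power is about 0.71.

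**6. The ICC implied by the limit.** (m − 1)ρ ≤ 0.25, so:
- m = 40 enrolled per class: ρ ≤ 0.25/39 = 0.0064
- m = 32 completers per class (40 × 0.80): ρ ≤ 0.25/31 = 0.0081

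**7. Dependence on the effect size.** For two equal groups f = d/2, so d = 1.0 is f = 0.5, twice the f used. At f = 0.5 a total of 34 gives 80% power (0.805), and 102 effective cases give over 99%.

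**8. Degrees of freedom between classes.** Sections 2.4.2 and 2.10 have four classes, and section 2.13 assigns one to each factorial group. (One sentence in section 2.4.1 mentions eight selected classes; the rest of the article has four.) The model in section 2.13 includes both factors and their interaction, so the classes leave 4 − 4 = 0 degrees of freedom to estimate variation between classes. Steps 4 to 7 ignore this.

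**The case against.** Four points can be made for the plan.

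- **The limit of 1.25 is an upper bound, and the increase might be shared.** For example, 10% attrition with DE 1.125 gives 128 × 1.125/0.90 = 160. But section 2.10 states 20% attrition and derives 160 from it. At 20%, any ICC above zero takes the effective number below 128. The example's values are not in the document.
- **The section also assumes d = 1.0.** A reader might infer from the 71% that the trial is simply underpowered. The document does not support that without a condition: 71% holds for f = 0.25, whereas at f = 0.5 the same 102 effective cases would be ample. This stands and limits the power statement. It does not repair the inflation, because 128 was derived from f = 0.25 and the section never offers the larger effect as a reserve for clustering.
- **The ICC comes from a cited source that is not shown.** This also stands. The 0.0064 is what the stated limit requires; nothing in the document shows that the true ICC is larger.
- **Section 2.13 calls the trial a pilot and looks to effect sizes and confidence intervals.** This softens the risk of a misread null only in part, since its caution about non-significance concerns interaction tests.

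A reader might also infer that enrolling 200, or more at a larger assumed ICC, would restore 80% power. That does not follow. At 40 per class, 200 students are five classes, which do not divide equally over four arms. With the number of classes fixed at four, the effective sample cannot exceed 4/ρ however many students are added; at an assumed ICC of 0.05 that ceiling is 80. The 200 shows only what the section's own formula gives when applied consistently.

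**Conclusion.** The sample size statement is wrong as written. One 25% increase is used in full for attrition and again for clustering. On the section's own limits the consistent total is 200 rather than 160, and 160 students correspond to about 102 effective cases. The 128 is what remains after dropout before any design effect is applied.

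The double count rests only on the stated 20% attrition and on any design effect above 1.00. The figures of 200 and 102 further assume the design effect at its stated limit of 1.25, and the 71% also assumes f = 0.25. That limit implies an ICC of no more than 0.0064 at 40 per class (0.0081 at 32), which the reader cannot check because no value is given.

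The 80% power claim should not stand in any case. With one class per arm, class and group effects cannot be separated, so no design-effect calculation can support it. For the same reason, a table of power over a range of ICCs would replace one unsupported figure with several.

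**What to change.** In section 2.10:

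- Delete the sentences saying that 160 covers both attrition and clustering and still yields 128 cases after the design effect.
- State the ICC relied on, and apply the design effect and attrition one after the other, making clear which figure is a headcount and which an effective number.
- Settle whether d = 1.0 (f = 0.5) or f = 0.25 governs.
- Withdraw the 80% power claim, giving one class per arm as the reason, and describe the sample size on the pilot and feasibility basis that section 2.13 already states, so that the two sections agree.

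The cost is revised wording and a less favourable stated figure. No extra participants are needed.
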